**Data collection and management**

Study follow-up and the variables that will be collected are described below.

Baseline:

Demographics, comorbidities, medications, sequential organ failure assessment (SOFA) score [31], days of COVID-19 since symptoms initiation, characteristics of COVID-19 symptoms at debut and at hospitalization, date of hospitalization.

Hemodynamics: heart rate, systolic and diastolic blood pressure, temperature, peripheral arterial 02 saturation, respiratory rate, arterial blood gases.

Evolution:

SOFA criteria daily until day 30 or discharge

Temperature daily until day 30 or discharge

Hemodynamics daily until day 30 or discharge

Respiratory function daily until day 30 or discharge: oxygen requirements, type of support, daily SaO2/FiO2, PaO2/FiO2 on day 0, 3, 7, 14 and 21.

Register of vasoactive drugs until day 30 or discharge

Register of antibiotics, antivirals until day 30 or discharge

Register of steroids and other immunomodulators until day 30 or discharge

Register of anticoagulants and thromboprophylaxis until day 30 or discharge

All-cause mortality at hospital discharge, and at 30 days

Cause of death.

Laboratory:

Total lymphocyte count; C-reactive protein, procalcitonin, LDH, D-dimer, troponin, pro-BNP, ferritin and IL6 evolution on days 0, 3 and 7.

SARS-Cov2 PCR in nasopharyngeal swab and in plasma on days 0, 3 and 7.

IgG SARS-CoV-2 titers on days 0, 3 and 7.

SARS-CoV-2 neutralizing antibodies capacity on day 0.

Imaging:

High-resolution chest CT scan at enrolment (day 0), and at day 5. If the patient has a contraindication or is unable to undergo a CT scan, a portable chest X-ray will replace it. For CT analysis and interpretation we will use three previously validated imaging scores for COVID pneumonia severity^6–9^. For the radiologic analysis when a chest CT scan cannot be performed and is replaced by a portable chest X-ray, we will add a blinded thoracic radiologist expert evaluation for improvement, stability or worsening of lung infiltrates.

Quality control:

Several procedures will assure data quality, including (1) all investigators will have certified good clinical practices training, (2) data collection will be done daily exclusively by three trained clinical research nurses; (3) a data manager will check daily data provided in the CRFs for missing data, plausible, possible or non-permitted value ranges, and logic checks. (4) any of the inconsistencies or missing data will be notified to the clinical project manager and asked to correct them before entering data in the final electronic database; (5) the principal investigator will review detailed weekly reports on screening, enrollment, follow-up, inconsistencies and completeness of data.

**Sample Size**

Sample size was calculated with a power of 80% and a statistical significance of 5% for an expected primary outcome in 54.8% of the patients in the control group and 20% of patients in the intervention group (absolute risk reduction of 35%) based on a previous immune plasma experience in AH1N1 influenza^10^. The final calculated sample size was of 29 individuals per group (total n = 58)

**Statistical Analysis Plan**

Continuous variables will be shown as mean and standard deviation for normally data or median and interquartile range elsewhere. Categorical variables will be shown as the number of cases and percentages

Primary outcome

We will assess the effect of early plasma compared to delayed plasma on the primary binary outcomes through chi-squared tests or Fisher’s exact test when appropriate, and odds ratios will be presented together with 95% CI and p-values. In addition, as an exploratory analysis we will adjust for age and SOFA score at enrolment, and clinically significant baseline variables if they result imbalanced between both study arms, as fixed (individual-level) effects, using logistic regression. Values of p<0.05 (2 tails) will be considered.

Secondary outcomes

We will assess the effect of early plasma compared to delayed plasma on the secondary binary variables through chi-squared tests or Fisher’s exact test when appropriate. For continuous variables with normal distribution we will use the t-test, and for continuous variables with non-normal distribution the Wilcoxon-rank-sum test or Mann-Whitney U test for comparisons. Additionally, we will analyze binary variables using logistic regression. Numerical variables will be examined using generalized linear models with log link function and gamma family function. Treatment effects, crude and adjusted, will be presented as exponentiated coefficients, i.e. odds ratios, hazard ratios or incidence rate ratios, respectively and treatment effect estimates will be presented with 95% CI.

To test difference between Kaplan-Meier estimates in survival analysis, we will use the Log-Rank test and/or Cox proportional hazard models for time-to event variables.

For the analysis of paired continuous variables, we will use Wilcoxon matched-pairs signed-rank test.

Statistical significance will be defined using a 2-sided significance level of α = .05.

Immune response subgroup analysis

A pre-planned analysis of baseline neutralizing antibodies titers and anti-SARS-CoV-2 IgG titers progression (on days 0, 3, 7), is planned for participants from the early plasma group and for the subset of participants from the deferred plasma group who will not have yet received plasma on those scheduled days. Groups will be compared through Chi-squared tests or Fisher’s exact test when appropriate.

Statistical significance will be defined using a 2-sided significance level of α = .05.

The statistical analysis will be performed by an investigator who was blind to the study group allocation.

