**Secondary Outcomes:**

- Clinical: days of oxygen requirement; days in mechanical ventilation; days of high-flow nasal cannula (HFNC) requirement; multiple organ dysfunction score (SOFA) (day 0, 3 and 7); days in intensive or intermediate care unit (ICU); time to respiratory failure development (Pa0_2_/FiO_2_<200 or, if arterial blood gases are not available on that day, a sustained Sa02/Fi02< 214 will be considered equivalent); length of hospitalization; 30 day-mortality.
- Microbiological: SARS-Cov2 PCR clearance in nasopharyngeal swab (days 0, 3 and 7)
- Inflammatory markers kinetics: lymphocyte count, C-reactive protein, procalcitonin, lactate dehydrogenase (LDH), D-dimer, ferritin and IL-6 evolution on days 0, 3, and 7.
- Radiologic: chest CT scan pneumonia score or portable chest X-ray progression between days 0 and 5.

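### The day-3/7 comparisons name no day-0 value as covariate, the secondary adjustment set is unstated, and observed imbalance may add covariates to an exploratory primary model

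*Combined protocol and SAP*

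**What the plan says.** **Data collected.** Secondary Outcomes lists SOFA on days 0, 3 and 7, and marker kinetics that include "D-dimer, ferritin and IL-6 evolution on days 0, 3, and 7". Data collection and management schedules IgG titres on the same three days.

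**Secondary analysis.** Under Statistical Analysis Plan, continuous secondary outcomes are compared between arms by t-test or rank-sum test. Gamma regression with a log link is added, and both crude and adjusted effects are to be shown with 95% CIs. The adjusting variables are not named and the day-0 value is not mentioned. The plan also states: "For the analysis of paired continuous variables, we will use Wilcoxon matched-pairs signed-rank test". IgG progression is compared by chi-squared or Fisher test, in the early arm and in those deferred patients who have not yet had plasma.

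**Primary analysis.** The test is an unadjusted chi-squared or Fisher test, reported as an odds ratio. A logistic model, labelled exploratory, adjusts for age and enrolment SOFA and then for "clinically significant baseline variables if they result imbalanced between both study arms".

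**Sizing.** Sample Size works from an "absolute risk reduction of 35"%.

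**The concern.** A patient's day-0 value usually predicts the day-3 and day-7 values. An analysis that ignores it leaves that variation in the error term, which matters with 58 patients. If the covariates of the adjusted secondary analyses are unstated, they can be settled after the results are seen.

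A signed-rank test on paired data compares a patient with himself over time. In a parallel-group trial it shows change, not a plasma effect, because these markers can move without plasma. Run arm by arm, it invites the misreading that plasma worked because one arm's change was significant and the other's was not.

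Choosing covariates by observed imbalance makes the adjusted primary estimate depend on the data and takes no account of prognostic strength. Finally, a trial sized on an absolute difference should report that difference. An odds ratio alone looks like a larger effect than the corresponding risk ratio.

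**Working it through.** **Inputs from the documents.** Sample Size: 80% power, 5% significance, "54.8% of the patients in the control group and 20% of patients in the intervention group", and "29 individuals per group (total n = 58"). Statistical Analysis Plan: "Values of p<0.05 (2 tails) will be considered".

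**Inputs assumed, because the documents give none.** Baseline-to-follow-up correlation r of 0.3 to 0.7; 29 evaluable patients per arm on days 3 and 7; age and SOFA each with a log-odds of 0.5 or 1.0 per SD; 8 to 10 independent imbalance candidates; imbalance cut-offs of p<0.05 or p<0.10.

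**1. The plan's own sample size.** With pooled variance under the null, two-sided, no continuity correction:

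n = [1.96·√(2·p̄(1−p̄)) + 0.8416·√(p₁(1−p₁)+p₂(1−p₂))]² / (p₁−p₂)²

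- 0.548 vs 0.200 (difference 0.348): n = 29.1, rounded up to 30. Power at 29 per arm is 79.8%.
- 0.548 vs 0.198 (the stated 35 points): n = 28.8, rounded up to 29.

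The plan's figure reproduces.

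**2. Value of the day-0 measurement.** Normal approximation, outcome SD = 1.

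- Follow-up-only comparison: the difference detectable with 80% power is (1.96+0.8416)·√(2/29) = 0.736 SD.
- ANCOVA multiplies the variance by 1−r².
- A change score has variance 2(1−r). The ratio of ANCOVA to change-score variance is therefore (1−r²)/[2(1−r)] = (1+r)/2.

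| r (assumed) | 1−r² | ANCOVA power at 0.736 SD | Detectable difference, 80% power | n per arm for 80% power at 0.736 SD | Variance saved vs change score |
|---|---|---|---|---|---|
| 0.3 | 0.91 | 83.6% | 0.70 SD | 27 | 35% |
| 0.5 | 0.75 | 89.9% | 0.64 SD | 22 | 25% |
| 0.7 | 0.51 | 97.5% | 0.53 SD | 15 | 15% |

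**3. The imbalance clause.** With 10 independent candidates, chance alone triggers at least one addition in 1−0.95¹⁰ = 40% of trials at p<0.05, and in 1−0.90¹⁰ = 65% at p<0.10.

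Simulated trials of 58 patients (4,000 per setting, 8 non-prognostic candidates, added when |z|>1.645):

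| Log-odds per SD, age and SOFA | Analysis | Power | Null rejection |
|---|---|---|---|
| 0.5 | Chi-squared | 78.7% | 4.6% |
| 0.5 | Age and SOFA | 83.3% | 6.2% |
| 0.5 | Age, SOFA and imbalance picks | 81.6% | 6.3% |
| 1.0 | Chi-squared | 78.4% | 4.5% |
| 1.0 | Age and SOFA | 90.2% | 5.4% |
| 1.0 | Age, SOFA and imbalance picks | 88.7% | 5.4% |

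The clause costs 83.3−81.6 = 1.7 and 90.2−88.7 = 1.5 power points and leaves null rejection essentially unchanged. Taking the most favourable of the three results would give about 8% false positives.

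**4. Signed-rank tests run by arm.** Suppose both arms change equally and plasma does nothing. If each arm's test is significant with probability p, exactly one arm is significant with probability 2p(1−p). Paired-t approximation, n = 29, change in SDs of the change:

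| Change | p | 2p(1−p) |
|---|---|---|
| 0.2 | 0.18 | 30% |
| 0.4 | 0.55 | 50% |
| 0.5 | 0.74 | 39% |
| 0.6 | 0.88 | 22% |
| 0.7 | 0.95 | 9% |
| 0.8 | 0.99 | 3% |

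**5. Effect measures at the design rates.** OR = (0.20/0.80)/(0.548/0.452) = 0.21; RR = 0.20/0.548 = 0.36; risk difference = 34.8 points.

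**6. Room for covariates.** Expected events: 29·0.548 + 29·0.20 = 21.7, about 22.

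**The case against.** The plan is better than a quick reading suggests, and several stronger readings fail.

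- **That covariates enter the primary model only through imbalance.** They do not: age and enrolment SOFA are named in advance.
- **That the imbalance clause compromises the primary result.** It sits in a model labelled exploratory. The primary test is unadjusted, and the plan says the analyst is blind to allocation. What remains is that nobody can say beforehand which adjusted model will be reported.
- **That baseline adjustment is excluded from the secondary analyses.** Adjusted gamma-model effects with CIs are promised, so the gap is an unnamed covariate set. IgG is not tested by t or rank-sum, and seroconversion is itself defined against baseline.
- **That the signed-rank test is offered as evidence for plasma.** The plan never says so, and it has separate between-arm tests. The risk of discordant arms also depends heavily on the size of the change, from 50% down to 3% in the table, and the documents give no expected change.
- **That the full gain over follow-up-only testing is certain.** The tested quantity is not stated. If change scores are meant, the saving is the smaller one at high r. Discharge and death before day 7 will also leave fewer than 29 per arm, by an unknown amount.
- **That an adjusted estimate should replace the primary test.** A model-standardised risk difference rejected a true null in 5.4% to 7.4% of simulated 58-patient trials, depending on the run and on whether two or three covariates were used. Chi-squared gave 4.5% to 4.9%. That trade-off is debatable and is not recommended here.

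Counts and percentages are already planned, so a reader could derive the risk difference, but its confidence interval should be reported directly.

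**Conclusion.** The point holds in a limited form and is a free improvement, not an error that invalidates the trial. The day-0 value is collected but named in no between-arm comparison of days 3 and 7, and the secondary adjustment set is open. Using the day-0 value would raise 80% power to about 84%, 90% or 98% at r = 0.3, 0.5 or 0.7. Against change scores it would save 35%, 25% or 15% of the variance. These figures assume 29 evaluable patients per arm and the stated correlations.

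The imbalance clause leaves the primary test untouched and has a small cost, 1 to 2 power points under the simulated settings. Its fault is that it leaves the adjusted model to be chosen from the data. Signed-rank results describe within-patient change and cannot show a plasma effect.

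**What to change.** (a) Analyse day-3 and day-7 SOFA and markers (log scale where skewed) by ANCOVA or a repeated-measures model containing the day-0 value, arm, day and arm-by-day. Report the between-arm effect with its 95% CI. Do the same for log IgG titre within its planned subset, noting that baseline adjustment does not undo the selection of deferred patients not yet given plasma. Label signed-rank results descriptive.

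(b) Delete the imbalance clause. Keep age and enrolment SOFA as the fixed covariates of the adjusted primary model, since about 22 expected events allow few more. Leave the chi-squared or Fisher test as the primary test.

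(c) Report the risk difference with its 95% CI beside the odds ratio.

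Cost: SAP wording and a little more analysis work. No new data and no extra patients are needed.

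### The SAP's supplementary logistic models have no small-sample or zero-cell method for 58 patients: the exploratory adjusted primary odds ratio would be moderately exaggerated if plasma works, and a sparse secondary outcome may have no usable odds ratio

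*Combined protocol and SAP*

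**What the plan says.** Under Statistical Analysis Plan, Primary outcome, the main comparison is a chi-squared or Fisher's exact test, reported with an odds ratio, its 95% CI and a p-value. As an exploratory step, a logistic model follows: "we will adjust for age and SOFA score at enrolment, and clinically significant baseline variables if they result imbalanced between both study arms". Age and SOFA are fixed. The number of further covariates is open.

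Under Secondary outcomes, binary variables are compared by chi-squared or Fisher's test. The plan then adds: "Additionally, we will analyze binary variables using logistic regression". It says that crude and adjusted effects will be given as exponentiated coefficients with 95% CIs. The binary candidates in the Secondary Outcomes list are 30-day mortality and PCR clearance, and no event rate is given for either.

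The Sample Size section expects the "expected primary outcome in 54.8% of the patients in the control group and 20% of patients in the intervention group", with 29 patients per arm.

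The documents name no estimator for the logistic models. They give no penalised or exact logistic method, no rule for zero cells or separation, and no cap on covariates.

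**The concern.** Unqualified logistic regression normally means maximum likelihood (ML), which has two known weaknesses in small samples. With few events per model term, the estimated log odds ratio is biased away from zero whenever there is a true effect. When one arm has no events, the estimate is not finite and its Wald interval has no meaning.

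The plan provides Fisher's test for small cells on the testing side but nothing equivalent for the estimates. The adjusted odds ratio would tend to exaggerate a real effect, and more so with each imbalanced covariate added. If a secondary outcome proved sparse, the analyst would have to choose a rescue method after seeing the data.

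**Working it through.** **1. The plan's own figure.** Inputs from Sample Size: 54.8% v 20%, 80% power, 5% significance. The tests are two-sided according to the Statistical Analysis Plan ("Values of p<0.05 (2 tails) will be considered"). The pooled-variance formula without continuity correction is

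n = [1.960 × √(2 × 0.374 × 0.626) + 0.842 × √(0.548 × 0.452 + 0.20 × 0.80)]² / 0.348² = 29.1 per arm.

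This rounds up to 30. Power at 29 is 79.8%, and rounding the control rate to 55% gives 29. The stated size is reproduced.

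**2. Events per model term.** Expected primary events are 29 × 0.548 + 29 × 0.20 = 15.9 + 5.8 = 21.7. With arm, age and SOFA this is 21.7 / 3 = 7.2 per term. With two more covariates it is 21.7 / 5 = 4.3.

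**3. Crude bias.** The design odds ratio is (0.20/0.80) / (0.548/0.452) = 0.206, a log OR of -1.579. The exact expectation of the ML estimate over two binomials of size 29 is -1.659 (OR 0.190). The overstatement is 1.659 / 1.579 - 1 = 5%.

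**4. Adjusted bias, by simulation.** Each setting used 4,000 trials of 29 + 29 patients with standard-normal covariates, and marginal rates were held at 54.8% and 20%. Covariate strength (log OR per SD) is an assumption, because the documents give none. ML figures exclude the few fits that failed (at most 0.4% of those shown). Monte Carlo error of the bias is about 1 percentage point.

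| Covariates | Strength per SD | True log OR (OR) | ML mean log OR (OR) | ML overstatement | ML Wald coverage | Firth overstatement |
|---|---|---|---|---|---|---|
| 2 | 0 | -1.579 (0.206) | -1.746 (0.174) | 10.6% | 95.0% | 1.0% |
| 2 | 0.5 | -1.740 (0.176) | -1.944 (0.143) | 11.7% | 95.7% | 1.3% |
| 2 | 0.8 | -1.958 (0.141) | -2.206 (0.110) | 12.7% | 96.0% | 0.5% |
| 4 | 0 | -1.579 (0.206) | -1.829 (0.161) | 15.8% | 95.1% | 1.4% |
| 4 | 0.5 | -1.882 (0.152) | -2.248 (0.106) | 19.5% | 95.9% | 1.6% |
| 4 | 0.8 | -2.258 (0.105) | -2.794 (0.061) | 23.7% | 96.8% | 1.3% |

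Other runs with the same design agreed, giving about 10-13% with two covariates. Part of the mean bias is skewness: the median is overstated by about 5-8% with two covariates. In a further run, Firth's method lowered the root mean squared error from 0.79 to 0.68 with two covariates and from 1.02 to 0.75 with four. At a smaller effect (54.8% v 40%, two covariates at 0.5 per SD) the overstatement was 12.5% for ML and 3.5% for Firth.

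**5. No effect.** With two covariates at 0.5 per SD and no treatment effect (3,000 trials), the mean ML log OR was -0.015, which is within Monte Carlo error of zero. Coverage was 95.2% and the rejection rate 4.8%.

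**6. Zero-event arms.** For event rates a and b, P(at least one arm has no events) = 1 - [1 - (1-a)^29] × [1 - (1-b)^29]. The rates are assumptions. Here 0.95^29 = 0.226, 0.90^29 = 0.047 and 0.85^29 = 0.009.

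| Rates | Calculation | Chance |
|---|---|---|
| 5% / 5% | 1 - 0.774² | 40% |
| 10% / 5% | 1 - 0.953 × 0.774 | 26% |
| 10% / 10% | 1 - 0.953² | 9% |
| 15% / 15% | 1 - 0.991² | 2% |

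In these trials the crude OR is 0, infinite or, if both arms are empty, undefined. At 10%/5% with two covariates at 0.5 per SD, ML failed in 27.5% of simulated trials, while Firth gave a finite estimate in at least 99.9%. Firth understated the log OR there by 8.5% (-0.710 against -0.775).

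**The case against.** The strongest reply is that none of these models decides anything. The adjusted primary model is labelled exploratory, and the secondary logistic models come on top of chi-squared or Fisher tests. That stands. A reader might infer that the trial's main result is at risk. The documents do not support this, because the primary p-value does not come from a logistic model.

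The bias is also modest beside the noise. With two covariates, one run gave -0.17 against a standard deviation of 0.76, about 0.2 SD. Wald coverage stayed at 94-98% in every primary scenario examined. A reader might infer that the adjusted result will always look better, or worse, than the truth. It will not: the bias exists only if there is an effect, and there is no inflation of false positives. The larger percentages need four covariates, whereas the plan fixes only two.

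For sparse outcomes, a reader might infer that infinite odds ratios will be frequent, or that the mortality analysis could yield nothing. The first depends on rates the documents do not give. Eligibility requires a CALL score of at least 9, so a mortality of 5% or less cannot be presumed. The second is wrong, because counts, percentages and Fisher's p-value remain.

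Finally, a separation fallback plus a covariate cap would be a reasonable alternative, and Firth's method does not itself close the open covariate list. That also stands. What survives the objection is that the plan promises these odds ratios with intervals and does not say how to obtain them when ML performs poorly or fails.

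**Conclusion.** The point holds in a limited form. The SAP plans logistic models in 58 patients without a small-sample or separation method. That ML would be used is inferred from silence; it is not stated.

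If the design effect is real, the exploratory adjusted primary log OR would be overstated by about 10-13% with age and SOFA and about 16-24% with four covariates. These ranges rest on the plan's own event rates and on assumed covariate strengths of 0 to 0.8 per SD. For secondary outcomes, the chance of losing the crude odds ratio runs from 2% to 40% over assumed rates of 15%/15% down to 5%/5%. The primary test, coverage at the planned rates and the sample size are unaffected. Severity is lower and confidence moderate.

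**What to change.** In the Statistical Analysis Plan, under both Primary outcome and Secondary outcomes, specify Firth-penalised logistic regression with profile-likelihood 95% CIs for the adjusted primary model and for the crude and adjusted models of the secondary binary outcomes. Keep chi-squared/Fisher as the tests, and report counts beside every odds ratio.

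The cost is SAP wording only. Standard software fits the model, no patients or data are added, and 29 per arm stands. The downside is slight shrinkage, with some understatement when events are very few (8.5% of the log OR in the 10%/5% example). The simulations checked Firth's point estimate and Wald interval (coverage 96-97% at the planned rates). They did not check the profile-likelihood interval, which is recommended on general grounds.

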**Exclusion criteria**

(1) PaO2/Fi O2 less than 200 or need for mechanical ventilation at enrolment

(2) Coinfection with other potentially relevant respiratory pathogen on admission

(3) Pregnancy or lactation

(4) Known IgA Nephropathy or IgA deficiency

(5) Previous intravenous immunoglobulin or plasma administration within the last 60 days

(6) Previous transfusion reactions that justify plasma contraindication (e.g. severe allergy)

(7) Do not resuscitate indication

(8) Patients participating in another interventional study related to COVID-19

(9) Patients that under investigator criteria had any condition that makes them unsuitable for study participation.

* CALL score includes the following parameters: age (< or > 60 years old), lymphocyte count (< or >1000), LDH (≤ 250; 250-500; >500) and comorbidities. The following comorbidities are included in the original CALL score: hypertension, diabetes, cardiovascular disease, liver disease, asthma, chronic lung disease, HIV infection and malignancy for at least 6 months. We added to comorbidities obesity (BMI≥ 30), chronic renal failure (stage III-V), solid organ transplant (<6 months) or hematopoietic transplant (<1 year), and immunosuppressant or immunomodulators use. We specified HIV infection with CD4<200 and cancer under current systemic treatment or in advance stage (IV).

CALL score is intended to predict the risk of developing severe COVID-19 defined as: SaO2≤ 93%, tachypnea ≥30 rpm, PaO2/FiO2 ≤ 300 o mechanical ventilation. Probability of progression to respiratory insufficiency is <10% for a CALL score 4-6, 10-40% for a CALL score 7-9 and >50% for a CALL score 10-13 (PPV 15.1; NPV 0.57) [20].

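### The gamma log-link model planned for all numerical secondary outcomes has no valid likelihood at zero, and the plan gives no rule for patients with zero days of organ support

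*Combined protocol and SAP*

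**What the plan says.** Under Secondary outcomes, the Statistical Analysis Plan first sets out simple tests, including, "for continuous variables with non-normal distribution the Wilcoxon-rank-sum test or Mann-Whitney U test for comparisons". It then adds a modelling layer: "Numerical variables will be examined using generalized linear models with log link function and gamma family function". The sentence does not limit the model to strictly positive variables. The section continues: "Treatment effects, crude and adjusted, will be presented as exponentiated coefficients, i.e. odds ratios, hazard ratios or incidence rate ratios", each with a 95% CI.

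The clinical secondary outcomes include "days of oxygen requirement; days in mechanical ventilation; days of high-flow nasal cannula (HFNC) requirement", together with days in intensive or intermediate care and the SOFA score on days 0, 3 and 7. The exclusion criteria rule out patients with "need for mechanical ventilation at enrolment".

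Neither the protocol nor the SAP says how zero values enter the gamma model, offers a two-part or count model, or names the software. The intention-to-treat statement under Handling of missing data and dropouts covers the primary outcome analysis only.

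**The concern.** A gamma distribution puts all its probability on values above zero, so a zero has no usable gamma likelihood. Nobody is ventilated at entry, so every patient who never progresses to ventilation contributes a zero to ventilator days. Zero is also a possible value for high-flow, oxygen and ICU days and for SOFA.

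For these outcomes the gamma model is the only stated route to a crude or adjusted effect with a confidence interval. If it will not run, the analyst has to choose a workaround after the data are in: drop the zeros, add a constant, or change the model. Dropping zeros is the most damaging choice. It conditions on an event that occurs after randomisation and that treatment is meant to prevent, and it removes more patients from one arm than from the other.

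**Working it through.** **1. Inputs.** Composite primary outcome rates of 54.8% (control) and 20% (early plasma), and 29 patients per arm, from Sample Size. Ventilation is one component of the composite, from Primary Outcomes. No ventilation at entry, from Exclusion criteria. The plan states no figure for the gamma model itself.

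**2. The plan's own figure.** With the usual two-sided pooled-variance formula,

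n = [1.96·√(2·p̄·(1−p̄)) + 0.842·√(p₁(1−p₁) + p₂(1−p₂))]² / (p₁−p₂)²,

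p₁ = 0.548 and p₂ = 0.20 give 29.1, rounded up to 30. Using the rounded 35-point difference (p₂ = 0.198) gives 28.8, rounded up to 29. Power at 29 per arm for 54.8% versus 20% is 79.8%. The stated 29 per arm is reproduced, so these are the rates the plan works with.

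**3. Expected zeros in ventilator days.** A patient without the composite was not ventilated and so has zero ventilator days.
- Control: 29 × (1 − 0.548) = 13.1
- Early plasma: 29 × (1 − 0.20) = 23.2
- Total: 36.3 of 58 = 62.6%

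This is a floor under the planned rates, because the composite can also be met by a stay over 14 days or by death without ventilation. If early plasma had no effect and both arms ran at 54.8%, the floor would be 2 × 13.1 = 26.2 of 58, or 45.2%. The same calculation cannot be made for high-flow, oxygen or ICU days or SOFA, because no rates are given.

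**4. The gamma density at zero.** The log-density at 0 is −∞ for shape 2, 0 for shape 1 and +∞ for shape 0.5. There is no generally valid likelihood contribution from a zero.

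**5. Software behaviour.** Two packages were tried on data containing zeros.
- R's Gamma family stopped with an error that non-positive values are not allowed.
- Python's statsmodels kept all 58 patients and converged. It returned the ratio of arithmetic means, but with an infinite log-likelihood; in effect this is a quasi-likelihood fit.

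**6. What dropping zeros would do.** Illustrative simulation with 29 per arm and the planned rates. Two assumptions are not in the documents: every composite event involves ventilation, and ventilated patients in both arms have the same duration distribution (gamma, shape 2, mean 10 days). The true ratio of mean ventilator days is then 0.20/0.548 = 0.36. About 29 × 0.548 + 29 × 0.20 = 15.9 + 5.8 = 21.7 patients are non-zero. Over 1,976 usable runs:

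| Analysis | Median ratio | Runs with p < 0.05 |
|---|---|---|
| Gamma log-link fit, zeros kept | 0.36 | 50% |
| Gamma log-link fit, zeros dropped | 0.99 | 8% |
| Rank-sum test, zeros kept | – | 77% |

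A second run of the same set-up (1,498 usable runs) gave 0.35 and 1.00.

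**7. The label.** The plan lists "odds ratios, hazard ratios or incidence rate ratios, respectively". Odds ratios belong to logistic regression and hazard ratios to Cox models, which leaves incidence rate ratios for the gamma model. Its exponentiated coefficient is a ratio of means.

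**The case against.** The strongest reply is that little is lost in practice. The section already plans a rank-sum test, which accepts zeros, and the gamma model comes only in addition. Software that accepts zeros gives a sensible crude answer: with a log link and treatment arm as the only covariate, the fitted mean in each arm is the arm mean, whatever the variance function. In a made-up example with 66 total ventilator days in 29 controls and 41 in 29 early-plasma patients, the gamma-type fit and a quasi-Poisson fit both give 41/66 = 0.62, with matching robust intervals. The primary outcome is binary and is analysed separately. All of this stands, and it limits the severity.

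It does not remove the defect. A rank-sum p-value carries neither an effect size nor an adjustment, and the plan promises both with a 95% CI. Whether the model runs at all depends on software the plan does not name. Agreement between the two fits is guaranteed only without covariates.

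Four stronger readings are tempting but unsupported.
- **That zero-day patients will be dropped silently.** Nothing in the plan says zeros will be removed, and neither package tested did so.
- **That dropping zeros would systematically reverse the effect.** The documents give no ventilation durations. With equal durations in both arms the effect is erased on average. In the second simulation the direction flipped in 48% of runs, but that is chance scatter around a ratio near 1.
- **That most patients will also have zero high-flow or ICU days.** Such zeros are possible, but their share cannot be derived.
- **That zero ventilator days marks the patients who did best.** A patient can die without being ventilated.

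**Conclusion.** The concern holds as a moderate issue. As written, the plan assigns to several listed outcomes a model that is undefined at a value they can take. For ventilator days that value is expected in at least about 63% of patients on the planned rates, or 45% if the control rate applied to both arms. The floor rests on the planned composite rates. The 0.36-to-0.99 figure also rests on the two simulation assumptions and shows what a positives-only workaround would do; it does not predict what the analyst will do.

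The reach is limited to effect estimates, confidence intervals and adjusted analyses of secondary outcomes that can be zero. The primary analysis and the unadjusted rank-sum comparisons are untouched. The incidence-rate-ratio label is a naming error and does not change the number.

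**What to change.** For every outcome that can be zero (ventilator, high-flow, oxygen and ICU days, and SOFA), replace the gamma model with a log-link quasi-Poisson model, or an equivalent quasi-likelihood, with robust standard errors. Fit it in all randomised patients, zeros included, using the covariates already planned for adjustment. Keep the gamma model for strictly positive variables. Report the exponentiated coefficient as a ratio of means, and name the software. Keep the rank-sum test as planned.

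Moving to support-free days or a proportional-odds model is optional. It would change the estimand of the listed outcomes and is not needed to cure this problem.

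The cost is one paragraph of SAP wording and no new data. One limitation should be stated in the plan: robust standard errors are approximate with 29 patients per arm, particularly when few patients in an arm have non-zero values.
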